### Recruitment and consent

The patient will be informed about the RODEO-trial following placement of a syndesmotic screw or when he or she visits the outpatient clinic following surgery and is provided with the patient information letter. Patients will have a minimum of 2 days to decide whether they want to participate or not in the study. For patients recruited directly postoperatively this means they can be included upon their first visit at the outpatient clinic. For patients who are informed for the first time at the outpatient clinic the coordinating investigator will contact them by phone (if the patient agrees to be contacted by phone by the coordinating investigator). Randomisation will take place after they have returned the signed informed consent forms.

### Benefits and risks assessment, group relatedness

A recent systematic review suggests that our intervention is safe and has similar functional outcome compared to the routine removal [21]. Subjects will not undergo additional investigations and interventions due to participation in the RODEO-trial and therefore risks to subjects involved in this trial are at least similar to current practice. Potential benefits for subjects in the investigational treatment arm could be a lower risk of surgical site infections and not having to undergo a secondary procedure.

### Indemnities

The institutional review board at the AMC has waived liability insurance, because no additional risk can be attributed to participation in this study.

### Publication plan

The principal investigator, the study designer and the study coordinator will be named author. All others will obtain group authorship in the study group. All authors including group members are allowed to present the results after approval of the principle investigator.

## Discussion

Displayed above is the protocol for an adequately powered study investigating the difference in routine removal versus removal on demand of the syndesmotic screw in ankle injuries. This will be the first RCT able to prove whether a statistically significant and clinically relevant difference exists.

Since this is a pragmatic trial, surgeons are allowed to choose their own postoperative treatment routine. This, combined with the 15 participating centres will result in a variation in for example the use of a cast, the duration of non-weight bearing mobilisation and a minor variation in the timing of the removal of the syndesmotic screw. However, we believe that this situation accurately reflects daily practice, considering that slight variations in post-operative treatment regimens are inevitable.

The inclusion of the University Hospital Helsinki makes this trial international. This greatly improves the external validity of the trial. Not all secondary outcome measures can be used in an international setting. The budget impact analysis and the health care resources utilization for example can only be used for patients in the Netherlands. This is due to practical feasibility but also to ensure a valid outcome. When the same (translated) questionnaire would be used in patients in Finland, results would not be extractable since the costs of healthcare (e.g. a surgical procedure or a visit to the physiotherapist) will not likely be the same as in the Netherlands. However, the participation of a hospital outside of the Netherlands will give us more insight in how to implement the results not just in the Netherlands, but in the rest of Europe as well.

If this trial proves that removal on demand is indeed non-inferior to routine removal of the syndesmotic screw(s) in terms of functional outcome, this will offer a strong argument to adopt this as standard practice of care. It would mean that patients will not have to undergo a secondary procedure, leading to less complications and subsequent lower costs.

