**Discussion:**

If removal on demand of the syndesmotic screw is non-inferior to routine removal in terms of functional outcome, this will offer a strong argument to adopt this as standard practice of care. This means that patients will not have to undergo a secondary procedure, leading to less complications and subsequent lower costs.

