### Interventions

Patients will be informed about the study by their treating physician following the procedure in which the syndesmotic screw was placed. After this, patients are contacted by the coordinating investigator to request participation in the study. After obtaining signed informed consent patients will be randomly assigned in a 1:1 allocation ratio to one of the following groups:Control group: Routine removal of the syndesmotic screw(s) 8 – 12 weeks following the index procedureor2)Intervention group: On demand removal of the syndesmotic screw(s)

Patients in the control group will undergo routine removal of the syndesmotic screw 8 – 12 weeks post-operatively (according to the preference of the treating surgeon). Patients will not undergo routine removal in case of 1) a contra-indication for undergoing a second procedure for example due to a (new) medical condition or 2) explicit request of the patient after consultation of their treating surgeon. In the intervention group the screw will only be removed in case of symptomatic implants, defined as: 1) implants causing pain, 2) implants (suspected of) causing restricted range-of-motion 3) explicit request of the patient 4) an infection or 5) other problems related to the screw such as protruding screw-head. The screw will only be removed after a consultation of the treating surgeon (except in patients who wish to no longer participate in the study). In patients in the control group in whom the syndesmotic screw brakes prior to planned removal, the screw will be left in place and only removed in case of symptoms.

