### Primary Outcome

The primary outcome parameter is functional outcome 12 months following the index procedure measured with the Olerud-Molander ankle score (OMAS) (Table 2).

**Table 2 Tab2:** Time table and follow-up schedule

RODEO-trial	Enrollment	Randomization / Allocation	Follow-up		
TIMEPOINT	Post-operatively	8 – 12 weeks post-operatively	3 months Post-operatively	6 months Post-operatively	12 months Post-operatively
Enrollment					
Eligibility screening	X				
Informed Consent	X				
Intervention					
Removal of syndesmotic screw (according to randomization)		X			
Assessment					
Plain radiographs	X		X		
OMAS			X	X	X
Visual analogue pain scale (VAS)			X	X	X
Range-of-Motion			X	X	X
POWI			X		
AOFAS			X	X	X
EQ-5D-5 L			X	X	X
i-MCQ			X	X	X
i-PCQ			X	X	X

To be able to assess the Minimally Clinical Important Difference of the OMAS, anchor questions will be added to the OMAS at six and 12 months as described by Walenkamp et al. [23].

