### Secondary outcomes

#### Secondary outcome measures of the study are:

Functional outcome with the American Orthopedic Foot and Ankle Hindfoot Score (AOFAS) [24]Pain as measured by a ten-point Visual Analog Scale.Range of motion, both absolute and as a percentage compared with the uninjured side.Postoperative wound infections classified using the criteria as defined by The Centers for Disease Control and Prevention (CDC-criteria) [25]Synostosis or recurrent diastasis (as seen on radiographs made in case of symptoms)Health-related quality of life as measured by the EQ-5D-5 L questionnaire [26].Health care resources utilization (including amongst others; number of visits to the general practitioner and use of home care organizations) as measured by way of a combination of the Dutch/English iMTA Medical Consumption Questionnaire (iMCQ) and iMTA Productivity Cost Questionnaire (iPCQ) (only applicable for the Dutch study population).Costs (economic evaluation including budget impact analysis): the economic evaluation of the RODEO-trial will be performed as a cost-effectiveness (CEA) as well as a cost-utility (CUA) analysis (only applicable for the Dutch study population).

Furthermore general demographics will be assessed such as age, gender, body mass index, co-morbidities, American Society of Anesthesiologists (ASA) classification, substance abuse, level of activity, bone mineral density (when available), fracture characteristics, surgical characteristics, duration of non-weight bearing period and use of physiotherapy.

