### Statistical analysis

The primary endpoint will be analysed according to the intention-to-treat and the per-protocol principle, non-inferiority will only be declared if both types of analysis prove non-inferiority. The primary endpoint will be analysed using a one sided test for non-inferiority with an alpha of 0.025. Descriptive methods will be used to assess quality of data, homogeneity of treatment groups and endpoints. Normality of the data will be analysed by visually inspecting the histograms. Secondary outcomes will be analysed using either a t-test or Mann-Whitney U test for continuous data according to the distributing of the data and a Chi Square test for categorical data. Missing data will be handled through multiple imputation with predictive mean matching. All analyses will be performed using the standard statistical software. Separate analyses will be performed on subgroups based on age. A multivariable analysis will be performed to identify predictors of worse functional outcome.

The CEA and CUA will be performed on the intention to treat data, with a time horizon of 12 months and from a societal perspective. The primary economic outcomes are the costs per quality adjusted life year (QALY) and the costs per point functional recovery improvement. Moreover a budget impact analysis (BIA) will be performed with a time horizon of 4 years. The questionnaires estimating the secondary outcome measures ‘resources utilization’ and ‘costs’ will only be used in patients included in the Netherlands due to practical feasibility and to ensure a valid outcome.

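### The pre-stated conclusion that on-demand removal spares a second procedure and reduces complications is only partly covered by the listed outcomes, and the infection schedule tilts that comparison towards on-demand removal

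*Protocol article*

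**What the plan says.** The Discussion draws its practical conclusion in advance. If non-inferiority is shown on function, "It would mean that patients will not have to undergo a secondary procedure, leading to less complications and subsequent lower costs". The abstract repeats it: "This means that patients will not have to undergo a secondary procedure, leading to less complications and subsequent lower costs".

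The result that triggers this conclusion concerns function alone: "The primary outcome parameter is functional outcome 12 months following the index procedure measured with the Olerud-Molander ankle score (OMAS").

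Under Interventions, "In the intervention group the screw will only be removed in case of symptomatic implants", and five qualifying reasons follow: pain, restricted motion, patient request, infection, or another screw-related problem. The same section lets routine-arm patients keep the screw because of a contra-indication, at their own request, or because it broke before planned removal.

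Among the secondary outcomes, two are complications: "Postoperative wound infections classified using the criteria as defined by The Centers for Disease Control and Prevention (CDC-criteria") and "Synostosis or recurrent diastasis (as seen on radiographs made in case of symptoms"). Resource use and costs are also listed, but those questionnaires "will only be used in patients included in the Netherlands". Screw removal, reoperation and an overall complication rate are not in the list. In Table 2, removal appears only as the allocated intervention at 8 to 12 weeks, and wound infection (POWI) is marked at 3 months only.

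**The concern.** A non-inferior strategy needs an offsetting advantage to justify adopting it. Here that advantage is fewer operations and fewer complications; the section on benefits and risks names fewer surgical site infections and no secondary procedure as the potential gains. Neither follows from non-inferiority on the ankle score. How many procedures each arm undergoes is an empirical matter, because both arms permit departures from their nominal removal policy, yet no between-arm comparison of it is listed.

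The complication part does have listed outcomes, but infection is scheduled at a time that suits one arm better than the other. Routine removals cluster shortly before the single assessment, while on-demand removals can fall at any time up to 12 months. A lower infection count on demand could therefore partly reflect when infections were looked for, and the error runs in the direction of the conclusion already written.

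**Working it through.** The article gives no removal or complication rate, so it has no figure on this point to reproduce. The check sets the conclusion against the outcome list and the schedule.

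**1. Conclusion against listed outcomes**

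| Part of the conclusion | Listed outcome that bears on it | Limit |
|---|---|---|
| Second procedure avoided | None (no removal or reoperation rate) | Interventions permits removal on demand and retention in the routine arm |
| Fewer complications | Wound infection; synostosis or diastasis | Infection scheduled at 3 months only; synostosis or diastasis only on symptom-driven radiographs; no overall rate |
| Lower costs | Resource use, cost-effectiveness, cost-utility and budget impact | Dutch patients only |

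The Statistical analysis section applies a chi-square test to categorical secondary outcomes, so infection and synostosis or diastasis are compared between arms.

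**2. Timing of the infection assessment**

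Inputs: routine removal at 8 to 12 weeks (Interventions); one infection assessment at 3 months (Table 2), taken here as about 13 weeks; a follow-up window of 2 weeks (Study procedures), read here as either side.

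- Routine arm: the nominal visit falls 13 − 12 = 1 week to 13 − 8 = 5 weeks after removal. With the window, the extremes are 11 − 12 = −1 week and 15 − 8 = 7 weeks. Most routine removals therefore precede the visit, though a removal at week 12 could follow an early visit.
- On-demand arm: removal may occur at any time to 12 months. Of those months, 12 − 3 = 9 come after the only scheduled infection assessment. Study procedures describes the 6- and 12-month contacts as questionnaires plus range of motion.

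The expected number of infections after late on-demand removal is n × r × f × q, where n is patients in the arm, r the proportion with removal, f the share of removals after the 3-month visit, and q the infection risk per removal. The article gives none of r, f or q, so the direction of the bias can be stated but not its size.

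**3. Could a removal rate be estimated with the planned sample?**

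The abstract's total of 194 gives 194 / 2 = 97 per arm; with the 10% loss in the Sample size section, 97 × 0.9 ≈ 87 are evaluable. Assume an on-demand removal rate p of 10% to 40%, which is 9.7 to 38.8, or about 10 to 39, of 97 patients. The 95% half-width for one arm is 1.96 × √(p(1 − p)/87):

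- p = 0.10: 0.063
- p = 0.20: 0.084
- p = 0.40: 0.103

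For a difference between arms, the half-width is widest when both rates are 50%: 1.96 × √(2 × 0.25/87) = 0.149. These figures show attainable precision only; they do not measure harm.

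**The case against.** The strongest reply has four parts.

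- **Relevant outcomes are listed.** A reader might infer that the conclusion rests on no listed outcome at all. That is not so. Infection, the complication that the benefits section names, is listed and tested; synostosis or diastasis is listed; and costs have a full economic evaluation. With 14 of the 15 centres in Table 1 Dutch, the national restriction may matter little, although patient shares are not given. This part of the reply stands.
- **The sentence may be read too literally.** A reader might take it to promise that no on-demand patient will have a removal. It says that patients need not have one, and Interventions openly provides for removals. The assumed 10 to 39 patients are therefore not a count of broken promises. This stands too.
- **Removal status must be known anyway.** The per-protocol analysis cannot be run without it, and removals go through the treating surgeon. So the article does not show that removals go unrecorded. What it lacks is a named comparison, and the fix is cheap for the same reason.
- **This is a condensed article.** Complication logs may sit in the full protocol, and the infection outcome carries no explicit time limit. This stands only in part. The article presents its list as the study's secondary outcomes, fixes infection at one time in Table 2, and draws a conclusion that reaches further. Patients are told to attend sooner if signs appear, but that instruction is tied to the 3-month visit, and no infection documentation after it is described.

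**Conclusion.** The point holds in limited form. The listed outcomes support the pre-stated conclusion in part. The avoided-procedure element has no listed between-arm comparison, and the complication element rests on two specific outcomes, one of which is scheduled so that infections after routine removal are more likely to be found than those after later on-demand removal. The resulting bias favours the conclusion.

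Its size cannot be derived from the article. It would be negligible if on-demand removals were few, early or rarely infected, and would grow with each of those factors. The direction rests on two assumptions: that Table 2 is complete for infection, and that some on-demand removals occur after the 3-month visit.

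The primary non-inferiority analysis is untouched. The change is worth making because the conclusion is the practical argument for adopting the strategy.

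**What to change.** 1. Ascertain wound infection and other screw- or procedure-related complications, including screw breakage, through 12 months from the index procedure. Use the same method in both arms and both countries, drawing on hospital records and the existing 6- and 12-month contacts.
2. Add screw removal or other ankle reoperation by 12 months, with date and reason, as a secondary outcome for all patients.
3. Report each as a between-arm difference with a 95% CI.
4. In the abstract and the Discussion, make the statement about a second procedure and complications conditional on those estimates.

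The cost is additional outcome lines, an extended infection row in Table 2 and a short record review. No new visit or procedure is needed, and clinical management does not change.

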## Abbreviations

CEA: Cost-effectiveness analysis
CUA: Cost-utility analysis
EQ-5D: EuroQuality of Life-5D
iMCQ: iMTA medical consumption questionnaire
iPCQ: MTA productivity cost questionnaire
N: Number
NA: Not available
POWI: Postoperative wound infection
QALY: Quality adjusted life year
RCT: Randomised controlled trial
